## Abstract

**Introduction:**

Pregnancy is characterised by a high rate of metabolic shifts from early to late phases of gestation in order to meet the raised physiological and metabolic needs. This change in levels of metabolites is influenced by gestational weight gain (GWG), which is an important characteristic of healthy pregnancy. Inadequate/excessive GWG has short-term and long-term implications on maternal and child health. Exploration of gestational metabolism is required for understanding the quantitative changes in metabolite levels during the course of pregnancy. Therefore, our aim is to study trimester-specific variation in levels of metabolites in relation to GWG and its influence on fetal growth and newborn anthropometric traits at birth.

**Methods and analysis:**

A prospective longitudinal study is planned (start date: February 2018; end date: March 2023) on pregnant women that are being recruited in the first trimester and followed in subsequent trimesters and at the time of delivery (total 3 follow-ups). The study is being conducted in a hospital located in Bikaner district (66% rural population), Rajasthan, India. The estimated sample size is of 1000 mother-offspring pairs. Information on gynaecological and obstetric history, socioeconomic position, diet, physical activity, tobacco and alcohol consumption, depression, anthropometric measurements and blood samples is being collected for metabolic assays in each trimester using standardised methods. Mixed effects regression models will be used to assess the role of gestational weight in influencing metabolite levels in each trimester. The association of maternal levels of metabolites with fetal growth, offspring’s weight and body composition at birth will be investigated using regression modelling.

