**Figure 1 F1:**
[figure not shown]
Diagrammatic representation of the study hypothesis. We assume that the quantitative changes in maternal circulating metabolites are associated with gestational weight gain, and it influences fetal growth, offspring’s levels of metabolites, and body composition and anthropometric traits at birth.

Are quantitative changes in levels of metabolites associated with GWG during pregnancy?Are quantitative metabolic changes during pregnancy associated with fetal growth, offspring levels of metabolites and body composition at birth?

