### Study objectives

To detect differential changes in quantitative metabolites between the end of the first, second and third trimesters of pregnancy and to examine how these trajectories are associated with maternal weight gain.To determine the influence of metabolic changes during pregnancy on fetal growth, body composition (fat mass, lean mass and bone density) and anthropometry at birth (ie, body length, weight and circumferences) independent of maternal prepregnancy BMI and paternal phenotypic characteristics.To assess the association between maternal metabolic profile during pregnancy and metabolite levels of offspring at birth (in cord blood).

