#### Sample size

Studies of fairly large size for detecting associations between longitudinal changes in levels of metabolites in pregnancy and fetal growth, and levels of metabolites of the offspring at birth, are few in number. For example, Ciborowski *et al*
61 used 770 samples collected during the first trimester for studying the relationship between maternal metabolic levels with macrosomia and low birth weight. Maitre *et al*
58 investigated 34 metabolites on 438 samples recruited during the first trimester and found an association with fetal growth restriction and preterm birth. The majority of studies related to metabolic changes during pregnancy^62–64^ and maternal-fetal medicine^65 66^ were based on 30–60 samples.^67 68^ Exact power calculations are challenging due to a restricted number of prior studies leading to unknown features.^69^ Even the largest study on 4212 participants for studying the predictive metabolomic biomarker for placental complications included limited sample of pre-eclampsia (n=134), fetal growth restriction (n=162) and controls (n=259).^17^ Thus, the proposed sample size must be larger than the majority of informative studies conducted to date and feasible within the cost boundaries for the technology being used.

Tynkkynen *et al*
70 studied quantitative urine and serum metabolite data on 995 samples of Northern Finland Birth Cohort for establishing the proof of concept for conducting large-scale epidemiological studies in metabolomics using an example of BMI. A relatively large study (n=800) has found that maternal urine metabolites can independently explain 12% of birth weight after adjusting for all other lifestyle/clinical factors.^16^ They also found an association of trimester-specific metabolic changes on fetal weight (change of 1.2% in first trimester and 2.4% in third trimester). Studies have observed that a metabolite level may change from 10% to 30% (even more for some metabolites) from first trimester to third trimester.^15 71^

For a cross-sectional analysis, a sample size of 1000 will be sufficient (with 98% power) to explain 4%–5% variation in the level of a metabolite by maternal weight as a predictor, even after correcting for multiple testing (α= 0.0001; for number of metabolites). Moreover, a sample size of 1000 will also be sufficient to explain 2% variation in the fetal growth parameters (with 80% power, α=0.0001) by maternal level of metabolite as a predictor.

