### Data analyses

The evaluation of cross-sectional associations of maternal body weight with quantitative metabolite levels in each trimester, independently, will be done using regression-based modelling. Both level of metabolites and gestational weight in each trimester will act as exposure as well as outcome. Variables like socioeconomic position, gestational age, parity, diet, smoking and physical activity will be considered as confounders. Maternal characteristics will be considered as exposures (like trimester-specific weight, metabolite levels) to evaluate their association with offspring-related outcomes (fetal growth, birth weight, body compositions and metabolite levels). The potential confounders for maternal-offspring associations will be socioeconomic position, gestational age, parity, diet, sex of the offspring, smoking and physical activity.

Mixed effects regression models for repeated measures will be applied for examining longitudinal associations of weight gain from first to third trimester^42^ with maternal levels of metabolites during pregnancy and fetal growth.^105^ We will also analyse the associations of level of metabolites from first to third trimester with trajectories of GWG. Mediation analyses will be conducted for evaluating the role of maternal metabolites as intermediates between GWG and offspring’s body composition.^106^ False discovery rate based multiple testing correction for number of metabolites will be applied.^107^ Mediation analysis will be conducted to examine whether the effect of GWG on fetal growth is mediated through alteration in levels of circulating metabolites.

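### The abstract and the Data analyses section disagree on whether the mixed models use weight or weight gain, and neither confounder list names starting weight

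*Protocol article*

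**What the plan says.** The questions concern gain:

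- Abstract, Introduction: "our aim is to study trimester-specific variation in levels of metabolites in relation to GWG".
- Research question 1 (beside Figure 1): "Are quantitative changes in levels of metabolites associated with GWG during pregnancy".
- Objective 1, on the metabolite trajectories: "to examine how these trajectories are associated with maternal weight gain".

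The analyses name two different exposures:

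- Abstract, Methods and analysis (mixed models, weight): "Mixed effects regression models will be used to assess the role of gestational weight in influencing metabolite levels in each trimester".
- Data analyses (mixed models, gain): "Mixed effects regression models for repeated measures will be applied for examining longitudinal associations of weight gain from first to third trimester".
- Data analyses (separate regressions, weight): "The evaluation of cross-sectional associations of maternal body weight with quantitative metabolite levels in each trimester".
- Data analyses (both directions, weight): "Both level of metabolites and gestational weight in each trimester will act as exposure as well as outcome".
- Data analyses, offspring outcomes: weight in each trimester is again given as an example of a maternal exposure.
- Sample size, the 98% power statement: "variation in the level of a metabolite by maternal weight as a predictor".

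Data analyses also uses GWG for the trajectory analysis and for both mediation analyses.

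The confounders listed there are social position, gestational age, parity, diet, smoking and activity, with infant sex added for offspring outcomes. First-visit weight and BMI are in neither list. The strengths and limitations box says that prepregnancy measurements are lacking. Objective 2 nevertheless promises offspring results independent of prepregnancy BMI. Table 1 shows weight and height measured from the first visit, at weeks 10 to 13.

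**The concern.** Weight at a later visit is first-visit weight plus gain since then. Women usually differ more in how heavy they start than in how much they gain, so a coefficient for attained weight is mostly a comparison of heavier with lighter women. The article itself expects starting size to matter: its Introduction reports that high prepregnancy BMI goes with a disturbed maternal metabolome throughout gestation.

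Two things are at stake. If the abstract's wording is what gets fitted, or if the attained-weight regressions are read as evidence on GWG, a metabolite tied only to starting weight could pass for a gain signal, and a true gain effect could be hidden. If gain is fitted without starting weight, any correlation between the two carries the starting-weight effect into the gain coefficient.

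**Working it through.** **1. The plan's own power figure.** Inputs from Sample size: N = 1000, α = 0.0001, R² = 4–5%, predictor maternal weight, stated power 98%. Non-central F test of one coefficient, λ = N·R²/(1−R²), df 1 and 998, two-sided: power is 99.5% at R² = 4% and 99.96% at 5%. The figure is reproduced, slightly on the cautious side. It is for attained weight, as stated.

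**2. What attained weight measures.** Write W3 = W1 + G, where W1 is first-visit weight and G is gain to the third-trimester visit. The documents give no SDs, so these are assumptions: s1 = 7–11 kg for W1, sG = 2.5–4.5 kg for G, correlation ρ = −0.3 to 0.1.

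- Var(W3) = v = s1² + sG² + 2ρ·s1·sG
- R² of W3 on W1 = (s1² + ρ·s1·sG)² / (s1²·v)
- Lowest (7, 4.5, −0.3): v = 49 + 20.25 − 18.9 = 50.35; 39.55² / (49 × 50.35) = 0.634
- Middle (9, 3.5, 0): 81 / 93.25 = 0.869
- Highest (11, 2.5, 0.1): v = 121 + 6.25 + 5.5 = 132.75; 123.75² / (121 × 132.75) = 0.953

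The matching R² of W3 on G runs from 0% to 36%. At ρ = 0 the split is 71–95% for starting weight and 5–29% for gain.

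**3. Consequence in a third-trimester regression on attained weight (ρ = 0, N = 1000, α = 0.0001).**

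- Only starting weight matters, with R² = 5%: attained weight shows 0.05 × 0.708 = 3.5% to 0.05 × 0.951 = 4.8%. It is flagged with probability 98.4–99.9%.
- Only gain matters, with R² = 4–5%: attained weight shows 0.04 × 0.05 = 0.2% to 0.05 × 0.29 = 1.45%. Power is about 1–47%, against 99.5% or more with gain itself as the predictor.

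**4. Consequence in a mixed model on attained weight.** Simulation of a random-intercept model: 1000 women, three visits, 20 runs per scenario, SD of W1 9 kg, SD of gain 2.5 kg per interval, uncorrelated, random-intercept and residual SD 0.7 each. Entries are mean estimates (mean z).

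| True slope, W1 | True slope, gain | Attained-weight model | Gain slope, separate terms |
|---|---|---|---|
| 0.03 | 0 | 0.025 (9.6) | −0.002 (−0.3) |
| 0 | 0.03 | 0.004 (1.6) | 0.032 (4.8) |
| 0.03 | −0.03 | +0.020 (7.6) | −0.032 (−4.8) |

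The last row has the wrong sign for gain. Separate terms recover the gain slope to within about 0.002.

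**5. Gain alone, without starting weight.** In a single-visit regression on G that omits W1, the gain slope is shifted by b1·ρ·s1/sG, where b1 is the starting-weight slope. With s1 = 9 and sG = 3.5 this is −0.3 × 9/3.5 = −0.77·b1 at ρ = −0.3, zero at ρ = 0, and 0.1 × 9/3.5 = +0.26·b1 at ρ = 0.1.

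**The case against.** The strongest reply is that Data analyses is the fuller section and does give the mixed models weight gain; the abstract is a summary. The trajectory analysis and both mediation analyses also name GWG. The trimester-by-trimester regressions are openly described as cross-sectional associations of body weight, and in the first trimester nothing else is possible because no earlier weight exists. For that question, finding an association with weight is a correct result. The confounder list is worded as examples, and a condensed article may leave exact model terms to a fuller document. Every SD used above is assumed.

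Much of this stands. A reader might infer that attained weight is the only exposure and that the plan therefore cannot answer research question 1; the Data analyses section contradicts that. A reader might also infer that false hits from the weight regressions feed the mediation analysis; nothing says that those regressions select the mediators. Nor does the 98% power statement need relabelling, since it already says that it is cross-sectional with maternal weight as predictor.

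The reply does not remove three things: the two sections give different exposures for the mixed models; attained weight remains the stated exposure in the other regressions, including those for offspring outcomes; and a promise of independence from prepregnancy BMI has no stated variable behind it.

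**Conclusion.** The point holds as an inconsistency in the exposure combined with an unnamed starting-weight term. It does not show that the study fails to address its first question.

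If attained weight is fitted, its coefficient mainly reflects starting weight: about 63–95% of third-trimester weight variance over the assumed SDs and correlations. The exact share is uncertain, but starting weight dominates throughout that range. A gain effect can be missed (power about 1–47% when gain alone explains 4–5% of a metabolite, at zero correlation) or reversed, as in the simulated scenario with opposing slopes. If gain is fitted, as Data analyses says, this distortion does not arise, but confounding by starting weight stays possible unless that weight is in the model. Its size depends on a correlation that the documents do not give.

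**What to change.** - In the abstract, change *gestational weight* to *gestational weight gain*, so that it agrees with Data analyses.
- In the mixed models, and in the second- and third-trimester and offspring models used to answer GWG questions, enter first-visit weight (or BMI, since height is measured) and gain since the first visit as separate terms. Report the gain coefficient as the answer.
- State that first-visit weight or BMI stands in for the missing prepregnancy value in objective 2. It is a proxy, because weight at weeks 10 to 13 already includes any earlier change.
- Keep the cross-sectional attained-weight regressions if wanted, labelled descriptive and not read as evidence on gain.

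The cost is one extra model term, from data already collected, and some rewording. Gain estimates will be less precise than attained-weight estimates appear.

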**Ethics and dissemination:**

The study has been approved by the ethics committees of the Department of Anthropology, University of Delhi and Sardar Patel Medical College, Rajasthan. We are taking written informed consent after discussing the various aspects of the study with the participants in the local language.

Strength and limitations of this studyThis is a longitudinal study in India to examine trimester-specific metabolomic changes during the course of pregnancy and their influence on fetal growth.The study is collecting biological measurements on pregnant women during each trimester (first, second and third trimester) and their offspring at the time of birth.Newborns will be intensively phenotyped for the levels of metabolites and body composition.Unlike other Indian cohorts, the study participants are being recruited from a government hospital that caters for a rural population.Lack of information on prepregnancy measurements will restrict our analysis to the duration of pregnancy only.

## Introduction

The profound metabolic changes during healthy pregnancy ensure optimum fetal development and appropriate nutrient allocation between the mother and fetus.^1 2^ Such metabolic adjustments are required for meeting raised physiological needs of pregnancy and for providing additional energy to support labour and lactation.^1^ The concept of *‘the developmental origins of health and disease’* suggests that exposures during critical periods in utero can lead to *‘programmed’* structural and/or functional alterations that can transmit to the next generation and predispose them to disease at later age.^3 4^ A study on 115 women with normal pregnancy has found that higher circulating fatty acids are associated with lower blood pressure and more favourable metabolic phenotype of the mothers.^5^ The disparity in metabolic changes during pregnancy may influence fetal growth, and can increase the likelihood of adverse metabolic profiles across the life-course for both mother and the offspring through fetal programming.^6^ For instance, increased transport of glucose and free fatty acids to the fetal-placental unit can lead to adverse fetal growth (ie, macrosomia).^7 8^

The biological system-wide understanding of metabolism requires us to capture phenotypic changes of the human *metabolome*, which comprises the full spectrum of metabolites present in all cells, tissues or fluids of the human body,^9–11^ in different physiological states (ie, puberty, pregnancy, lactation and premenopause/postmenopause). The metabolome can be considered as an intermediate phenotypic mixture of metabolites encoded by our genome, influenced by specific environmental exposures and it shapes an individual’s *metabolic phenotype or* metabotype.^10–12^ It can be studied through the holistic approach of *metabolomics* that provides a quantitative fingerprint of all metabolites present in cells, tissues or an organism and can be measured using high-throughput technologies.^13 14^ The field of metabolomics is important for uncovering quantitative metabolic trajectories of normal and abnormal pregnancies. The studies on quantitative estimation of longitudinal metabolomic changes during gestation are globally few in number^15–17^ and there are none we know of in India.

### Metabolomic changes in pregnancy

The incomplete understanding of the complex nature of metabolic processes during pregnancy has generated considerable interest in exploring the effect of gestational characteristics on metabolomic changes during pregnancy and its impact on offspring health. Hyperglycaemia during pregnancy is one of the widely studied examples of pregnancy-induced metabolic stress which increases maternal risk of type 2 diabetes and also predisposes the developing fetus to poor metabolic health.^18^ Studies have also assessed the metabolomics of pregnancy complications, such as, gestational diabetes,^19 20^ placental abruption^21^ and birth outcomes, such as preterm birth,^22^ small for gestational age^23^ and large for gestational age.^24^

An exploratory study has investigated the changes in metabolite levels during pregnancy among women with gestational diabetes in the third trimester and found elevated levels of branched chain amino acids, leucine, isoleucine and valine.^25^ The catabolic nature of third trimester is represented by a decrease in maternal glucose levels and substantial rise in the levels of fasting insulin which in turn can lead to insulin resistance.^26^ Moreover, circulating levels of lipids and lipoproteins rise twofold to threefold in late pregnancy.^27^ Maternal amino acid levels change longitudinally due to placental uptake and fetal transfer from first to third trimesters.^15^ There is an increase in energy production through the TCA cycle during the course of gestation along with concomitant decreases in free carnitine and acetylcarnitine and increase in carnitine palmitoyltransferase-1 activity and β-hydroxybutyrate levels.^15^ A recent study has detected a role for metabolites in fetal sex differences in placental complications. It was found that higher maternal levels of spermine metabolite N1,N12-diacetylspermine (DiAcSpm), from the first to third trimesters, are observed in the female placenta and in the serum of women with a female fetus.^17^

### Relationships between maternal gestational weight gain and newborn health

Gestational weight gain (GWG) is a complex biological trait which is influenced by maternal physiology, maternal, placental and fetal metabolism.^28^ There are short-term or long-term implications of inadequate or excessive GWG which direct the trade-off between maternal and child health outcomes.^28–32^ For example, inadequate weight gain is associated with high risks of low birth weight, small for gestational age and preterm birth.^33^ Excessive GWG is associated with large for gestational age, gestational diabetes, caesarean section and postpartum weight retention.^34^ Furthermore, high prepregnancy maternal body mass index (BMI) is associated with perturbations to maternal metabolome across gestation.^35^

Maternal GWG is a good indicator of fetal nutrition.^36^ Any amount of weight gain in the first 14 weeks and high rate of weight gain (>500 g/week) in 14–36 weeks are associated with raised adiposity in the offspring.^37^ GWG in the first trimester is associated with offspring BMI from infancy to early childhood whereas excessive GWG (ie, ≥500 g/week) in second and third trimesters is associated with increased birth weight.^38^ In the first half of the pregnancy (<20 weeks), excessive GWG is associated with higher birth weight and high body fat in newborns compared with the second half of pregnancy.^39^ Furthermore, Gaillard *et al*
40 observed that early GWG was associated with increased adiposity levels and adverse cardiometabolic profile in childhood independent of prepregnancy weight. A study that investigated the effect of trimester-specific GWG on newborn anthropometry has found that women with an excessive rate of GWG in mid/late pregnancy deliver the heaviest babies.^41^ Thus, the role of optimum GWG in fetal and child health is well studied^42^ but the underlying biological mechanisms or mediating pathways are as yet unknown. The maternal fat deposition in early pregnancy due to excessive GWG may lead to maternal dysmetabolism^43 44^ and effect the levels of maternal metabolites in subsequent trimesters. A study has found that the levels of triglycerides, high-density lipoprotein-cholesterol, apolipoprotein A1 and interleukin-6 are linearly associated with GWG across all levels of GWG in mid-pregnancy.^37^ The authors postulated that mothers with high GWG may engage in lifestyles during and after pregnancy that may encourage weight gain. However, a few Indian studies have incorporated the GWG in their analyses, for example, an association of inadequate or excessive GWG with preterm deliveries,^45^ average GWG among women with gestational diabetes^46^ and maternal dietary intake of milk protein in first trimester on GWG.^47^ But there is no Indian study that has explored the association between GWG and levels of metabolites. The continuous variability in the amount of weight gain during pregnancy, with respect to parity, height and geography,^48–50^ has motivated the research for detecting the predictors and outcomes of GWG.

